
### Criteria for early withdrawal from treatment

4.3

Early withdrawal from treatment refers to withdrawal from the study treatment before the completion of the treatment course. Patients who withdraw from treatment early are not considered withdrawn from the study early and should continue to complete the follow-up visit process. The study will employ an intention-to-treat analysis, which includes all patients who were initially randomized to receive the study drug, regardless of whether they completed the full course of treatment. This approach ensures that the analysis reflects the provided treatment options’ real-world effectiveness. The criteria for early withdrawal from treatment are as follows:

The patient or their authorized person requests to withdraw from treatment;Patients whose conditions worsen or do not improve after 72 h of continuous use of the investigational drug and who have been determined by the researcher to no longer benefit from continued use of the investigational drug;After the investigational drug is applied, if the sample culture strain is resistant to the drug, the clinical efficacy is evaluated by the researcher as persistent or progressive;Individuals who experience intolerable adverse events/serious adverse events and for whom it has been determined by the researcher that continuing to use the investigational drug would pose a greater risk to the patient than its benefits;Cases in which protocol violations occur, such as receiving other effective antimicrobial treatments (excluding those specified in the protocol) or other concomitant medications prohibited by this protocol during the study period, which, in the judgment of the researcher, might seriously affect the elimination, metabolism, or efficacy evaluation of the investigational drug;Other situations that require early withdrawal from treatment.

### Exit criteria

4.4

All patients who signed a written informed consent form and were screened as qualified to enter the study had the right to withdraw at any time. The exit criteria were as follows:

The patient or their authorized person refuses to continue the study or voluntarily withdraws informed consent;Patient death;Patients who are lost to follow-up;Poor compliance, no longer accepting the medication or testing before completing all studies, or inability to adhere to the study protocol to complete the study;Other situations that the researchers believe require withdrawal.

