Outcome data	Survival at 30 days post randomization Date of death or discharge Total response (composite endpoint consisting of clinical cure and microbiological response) at the end of treatment and the test of cure visits Length of ICU stay and costs Protocol violations and adverse events Reasons for trial withdrawal

cIAI, complicated intra-abdominal infection; ICU, intensive care unit; APACHE, Acute Physiology and Chronic Health Evaluation; SOFA, Sequential Organ Failure Assessment; CRP, C-reactive protein; PCT, procalcitonin.

An independent Data Safety and Monitoring Board (DSMB) will be constituted to further enhance the safety and integrity of the study. The DSMB, comprising experts with pertinent knowledge and experience, will operate independently of the study team. Its remit is to conduct regular reviews of the accumulating trial data, to ensure the safety of participants and the validity of the trial results. The DSMB will have the authority to recommend to the sponsor whether to continue, modify, or stop the trial, based on its data review insights.

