## Statistics

11

This study is a randomized controlled clinical trial. The two groups are the eravacycline group and the tigecycline group, with a ratio of 1:1. All-cause 30-day mortality is the main outcome measure. The researchers plan to use noninferiority tests for the ratio of two propositions to estimate the required sample size, assuming a noninferiority ratio of 2. Owing to the lack of randomized clinical trials in this specific field, sample size estimates were obtained from Xavier Guirao et al.’s observational study on the treatment of intra-abdominal infections with TGC (16). In their study, the all-cause mortality of patients treated with TGC (our control group) was 18.7%. Our previous results revealed that the mortality rate of the eravacycline group (17.7%) was slightly lower than that of the tigecycline group, with an estimated actual ratio of 0.95. The total sample size calculated through PASS (version 15.0.5) is N = 262 cases to perform a unilateral analysis *α*, achieving 80% efficacy at a level of 0.025. Considering a 10% dropout rate, the total number of subjects required for the last two groups is 292, with at least 146 subjects in each group. In light of the considerable variability observed in ICU mortality rates, an interim analysis will be conducted once 50% of the data has been collected. This analysis will facilitate a reassessment of the effect sizes and power of the study. If the initial mortality rates diverge significantly from the anticipated estimates, the sample size will be adjusted accordingly to ensure the integrity and statistical power of the study are maintained.

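### Sections 4.3 and 4.4 conflict on whether a patient who declines study drug or does not adhere stays in follow-up, which puts 30-day survival, the primary endpoint, at avoidable risk of being missing

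*Protocol article*

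**What the plan says.** Section 4.3 (Criteria for early withdrawal from treatment) separates stopping treatment from leaving the study: "Patients who withdraw from treatment early are not considered withdrawn from the study early and should continue to complete the follow-up visit process". Its first listed reason is "The patient or their authorized person requests to withdraw from treatment". Protocol violations, such as receiving other effective antimicrobials, are also listed there as reasons to end treatment only. The same section commits to analysis by intention to treat, described as one "which includes all patients who were initially randomized to receive the study drug, regardless of whether they completed the full course of treatment".

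Section 4.4 (Exit criteria) lists the grounds for leaving the study. They are refusal to continue or withdrawal of consent, death, loss to follow-up, other situations judged by the researchers, and this item: "Poor compliance, no longer accepting the medication or testing before completing all studies". The item goes on to name patients who cannot adhere to the protocol.

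The endpoint at stake is stated in section 11 (Statistics): "All-cause 30-day mortality is the main outcome measure". Table 3 in section 10 lists "Survival at 30 days post randomization" among the outcome data.

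**The concern.** A patient who declines further study drug stays in follow-up under 4.3 and meets an exit criterion under 4.4. The same holds for a patient who does not adhere to the protocol. A site cannot follow both rules.

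If a site follows 4.4 and treats exit as the end of follow-up, 30-day survival may go unrecorded in patients who neither withdrew consent nor were lost. Refusing drug may well be related to tolerability or lack of response, poor compliance is not defined, and treating clinicians know the allocation (section 5). Such loss could therefore be informative. A later choice of analysis population cannot recover an outcome that was not collected.

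**Working it through.** **1. The two rules side by side**

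| Situation | Section 4.3 | Section 4.4 |
|---|---|---|
| Patient asks to stop study drug | Treatment ends, follow-up continues | Study exit (no longer accepts medication) |
| Protocol violation or non-adherence | Treatment ends, follow-up continues | Study exit (poor compliance, inability to adhere) |
| Worsening or no improvement after 72 h, resistant strain, intolerable adverse event | Treatment ends, follow-up continues | Not named |
| Consent withdrawn | – | Study exit (own item) |
| Lost to follow-up | – | Study exit (own item) |

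The conflict is confined to the first two rows. The 4.4 item joins medication and testing with *or*, so refusing the drug alone is enough. Because the last two rows have their own items, the compliance item only adds patients who can still be reached. Section 4.3 itself sets being withdrawn from the study against continuing the visits, so the natural reading of exit is that visits end.

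**2. The plan's sample size reproduces and is not affected**

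Inputs from section 11: control mortality p2 = 0.187, true ratio 0.95 (p1 = 0.95 × 0.187 = 0.17765), margin R0 = 2, one-sided α 0.025, power 80%, allocation 1:1. The Farrington–Manning score test for a ratio gives, per arm,

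n = [1.960·√V0 + 0.8416·√V1]² / (R0·p2 − p1)²

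- V1 = p1(1−p1) + R0²·p2(1−p2) = 0.7542.
- V0 is the same expression at the constrained estimates 0.2370 and 0.1185, which gives 0.5986.
- n = (1.516 + 0.731)² / (0.374 − 0.17765)² = 131.0, so 262 in total.
- Dropout: 262/0.90 = 291.1, rounded up to 292 (146 per arm).

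Both figures match the plan. At 131 per arm the exact power is 80.6%, and the exact chance of declaring noninferiority at a true ratio of 2 is 2.7%.

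**3. What missing survival could do at the planned rates (outer bounds)**

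Assumption: the whole 10% allowance, 15 per arm, has unknown status. Deaths seen among 131 per arm are 0.177 × 131 ≈ 23 and 0.187 × 131 ≈ 24. The ratio is 23/24 = 0.96, with an upper 95% limit of about 1.60, below 2.

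The complete-data ratio for 146 per arm then lies between:

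- 23/(24 + 15) = 0.59, if only the unseen tigecycline patients died; and
- (23 + 15)/24 = 1.58, if only the unseen eravacycline patients died. The upper limit is then about 2.50.

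The upper limit passes 2 once 7 of the 15 unseen eravacycline patients died and no unseen tigecycline patient did: 30/24 = 1.25, upper limit 2.03.

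**4. False noninferiority at a true ratio of 2**

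True risks are 0.374 and 0.187. A share d = 0.10 exits with mortality m, so the retained risk is (p − d·m)/(1 − d), with 131 retained per arm. Both d and m are assumptions. When exit in an arm is random, its retained risk is unchanged.

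| m | Retained eravacycline risk | Informative in eravacycline only (tigecycline 0.187) | Retained tigecycline risk, if also informative | Equally informative in both |
|---|---|---|---|---|
| 0.5 | (0.374 − 0.05)/0.9 = 0.360 | 4.0% | (0.187 − 0.05)/0.9 = 0.152 | 0.4% |
| 0.6 | 0.349 | 5.5% | 0.141 | 0.2% |
| 0.7 | 0.338 | 7.3% | 0.130 | 0.1% |

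Other scenarios:

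- Exited tigecycline patients have half the mortality of exited eravacycline patients: the figure stays at 2.7%.
- Exit is informative in tigecycline only: 0.2% or less.
- Only 2–3% exit under this clause, informative in eravacycline only: 2.9–3.6%.

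**The case against.** The strongest reply is that the article never says outcome collection stops at exit. Death is itself on the exit list, so the list partly records how participation ended. Table 3 asks for 30-day survival without excepting exited patients, and the full protocol may say how vital status is traced. This stands: loss of status is a risk that follows from the wording, not a stated rule. A reader might infer that 30-day survival is certain to be lost, or that intention-to-treat becomes impossible. The document supports neither. The analysis would be incomplete, and only if status is not sought.

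A reader might also infer that everyone who stops drug is affected. That is not so. Section 4.3 expressly keeps in follow-up those stopped for worsening, resistance or adverse events, the groups most clearly tied to a poor course or toxicity.

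One can also read the 4.4 item as disengagement from the study as a whole, since it speaks of completing all studies. That is plausible, but the *or* and the separate consent and loss items work against it.

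Nor can the 10% allowance be charged to this clause alone. It covers dropout in general, and no share for non-compliance is given.

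Finally, section 8 places the primary endpoint in the clinically and microbiologically evaluable populations, and the second of these already requires completion in line with the protocol. Many non-adherent patients might fall outside it anyway. The error rates above therefore illustrate an analysis of all randomised patients and are not a forecast for those two sets.

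**Conclusion.** The contradiction between 4.3 and 4.4 is real and stands in the printed text. It concerns patients who refuse study drug or do not adhere. It creates an avoidable, possibly informative, risk to the primary endpoint and to the intention-to-treat commitment.

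The tempting stronger claim, that the loss favours noninferiority, is not supported. It needs informative exit in the eravacycline arm alone (2.7% rising to 4.0–7.3%). Equal informative exit in both arms makes the test conservative (0.1–0.4%). The Discussion cites fewer discontinuations for adverse events with eravacycline (OR 0.17), which lends no support to heavier exit in that arm. All these figures assume a 10% exit share and 50–70% mortality among exits, and the document gives neither. The point should be corrected because the two rules cannot both be followed and the correction is cheap, not because a particular bias has been shown.

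**What to change.** Reconcile the two sections. Take poor compliance, non-acceptance of medication and non-adherence to the protocol off the study-exit list in 4.4, so that they count as treatment withdrawal under 4.3 with follow-up continuing. State that day-30 vital status is sought for every randomised patient, by visit, telephone or hospital record, unless consent to follow-up is withdrawn.

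This concerns follow-up and data collection only and does not touch when treatment should stop. The cost is a wording amendment and a day-30 status check for a few patients, on an item already in Table 3. The sample size is unchanged.

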## Test group

5

Patients who meet the inclusion criteria will be randomly assigned to the experimental group or control group at a 1:1 ratio. Tigecycline was chosen as a control drug because it is currently recommended by multiple authoritative guidelines/consensuses both domestically and internationally for the treatment of multidrug-resistant bacterial infections. In many countries, including the United States and China, tigecycline is commonly used in cases involving drug-resistant bacteria or other antibiotics and has poor efficacy for treating abdominal infections (11, 14, 15). Using a central stratified block randomization method, the subjects were randomly assigned to receive either eravacycline or tigecycline at a 1:1 ratio.

Although this study employs a single-blind design, we recognize the possibility of bias resulting from the clinicians’ awareness of the treatment allocation. To address this potential issue, we will include a blinded clinical assessor who will be unaware of the treatment assignments. The assessor will be responsible for conducting independent clinical evaluations and providing objective measurements in conjunction with the evaluations conducted by the investigators. This supplementary measure guarantees that a crucial element of our study remains free from bias, thereby enhancing the overall integrity of our findings. The remainder of the blinding procedure will adhere to the original protocol, ensuring that neither patients nor data analysis researchers are aware of the treatment groups, thus maintaining the integrity of the study.

When patients are registered after signing the consent form, detailed information about the anti-infective treatment, baseline demographics, and disease severity will be recorded before the start of the study.

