## Study design

2

This study is a multicenter, randomized, single-blind, tigecycline-controlled study involving 5 centers/hospitals. The trial was fully approved by the Ethics Committee of Ansteel Group General Hospital [(2023) Ethics Review No. (14)] and was registered in the Chinese Clinical Trial Registry^1^ with the listed primary and secondary endpoints. This study will be conducted in accordance with the clinical trial protocol (and any revisions), the Declaration of Helsinki (current revision), the international guidelines for the management of intra-abdominal infections, and the Chinese expert consensus (11, 12). The research design is shown in Figure 1.

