## Data management and monitoring

10

All raw data (Table 3) will be meticulously recorded in the Case Report Form (CRF) by designated researchers. To ensure accuracy, each data entry will be independently double-checked by two individuals. The research coordinator at each center will supervise the data collection process, and the chief investigator, database administrator, and the statistician responsible for the statistical analysis will jointly determine the optimal database location strategy.

**Table 3 tab3:** List of data collection methods.

	Variables
Demographic data	Date of birth, sex, height, weight
Trial characteristics	Dates of screening and enrollment, inclusion criteria and consent details, date and time of randomization
Past medical history and risk factors	Past 3 months’ medical history, concomitant diseases, surgical history, allergic history, medication history (including immunosuppressive drugs, cytotoxic drugs, and biological agents), participation in other drug or medical device clinical trials
Infection and prognostic assessment	cIAI diagnosis time, presumed source of infection, invasive operation for source control, adequacy of source control, residue lesions, ICU admission time, APACHE II score, SOFA score
Antibiotic data	After the onset of the disease, all antibiotic usage, type/time/dose/route/frequency information
Clinical observations	Daily vital signs (blood pressure, heart rate, respiration, body temperature), clinical symptoms and signs, urine output, hematological variables, renal variables, hepatic variables, coagulation function, blood gas analysis, CRP, PCT, use of vasoactive drugs, catecholamine index, use of renal replacement therapy, mechanical ventilation duration, concomitant medication
Microbiological data	Date and time of initial peritoneal drainage culture, full susceptibility profile, daily peritoneal drainage culture results days 1 to 4; any further positive peritoneal drainage cultures and pathogen detection/resistance characteristics; other clinical sites growing *Escherichia*, *Klebsiella* or *Acinetobacter*, any multidrug-resistant organism, *P. aeruginosa* or *Clostridium difficile* identified within 30 days

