### Analysis of the main effectiveness results

11.1

The purpose of this experiment is to evaluate the difference in treatment efficacy between the experimental group (eravacycline) and the control group (tigecycline). The statistical hypotheses are as follows: H_0_: P1/P2 ≥ R0 (the all-cause mortality rate of the experimental group is lower than or equal to that of the control group); H_1_: P1/P2 = R1 < R0 (the all-cause mortality rate in the experimental group is greater than that in the control group). The main efficacy indicator is the comparison of the all-cause mortality rate, which is a qualitative indicator and will be analyzed using the Pearson X^2^ test or Fisher’s exact probability method.

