### Analysis of secondary effectiveness results

11.2

The Pearson X^2^ test or Fisher’s exact probability method will be used to compare the differences between the two groups at different visit times and the proportion of total-response patients in different analysis populations. The length and cost of ICU hospitalization will be evaluated using independent sample t tests or Wilcoxon rank sum tests.

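### The crude tests fixed for 30-day mortality and total response use neither the randomisation strata nor the baseline APACHE II score, and so give up some precision

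*Protocol article*

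**What the plan says.** Section 5 (Test group) states: "Using a central stratified block randomization method, the subjects were randomly assigned to receive either eravacycline or tigecycline at a 1:1 ratio". The stratification factors are not named. Section 2 describes a "tigecycline-controlled study involving 5 centers/hospitals", but does not say that centre is a stratum.

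Table 3 in section 10 lists, under infection and prognostic assessment, "adequacy of source control, residue lesions, ICU admission time, APACHE II score, SOFA score". The table does not time APACHE II in its own row. Section 5, however, says that "detailed information about the anti-infective treatment, baseline demographics, and disease severity will be recorded before the start of the study", and section 11 defines baseline as the last non-missing value before the first dose of study drug.

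Section 11.1 fixes the primary analysis: all-cause mortality, "which is a qualitative indicator and will be analyzed using the Pearson" chi-square test or Fisher's exact test. Section 11.2 fixes the same two tests for response; they "will be used to compare the differences between the two groups at different visit times and the proportion of total-response patients". Neither section mentions strata or a covariate. The only stratified analyses in the article are the pathogen subgroups (CRAB and CRE) in section 8, and these do not adjust the primary comparison.

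**The concern.** The design stratifies the allocation and records severity before treatment, and the analysis then uses neither. If the strata or the score predict death, an unadjusted comparison carries outcome variance that could have been removed, and a chance imbalance in severity stays in the estimate. The expected number of deaths is small: 131 × 0.187 + 131 × 0.177 = 24.5 + 23.2, or about 48. The design also has little power in reserve beyond its 80% target.

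This is more than detail left to an analysis plan. The article names the test for the primary outcome, and that test cannot take strata or a continuous covariate. A plan that adjusted the primary analysis would have to depart from section 11.1.

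**Working it through.** **Inputs from the article (section 11).** Control mortality 18.7%; eravacycline mortality 17.7%, ratio 0.95; noninferiority ratio 2; one-sided α 0.025; power 80%; 262 patients, 292 after 10% dropout; 1:1 allocation.

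**1. Reproducing the plan's own figure.** The Farrington-Manning score test for a ratio gives n per arm = (1.960√V0 + 0.842√V)² / (R0·p2 − p1)², with p2 = 0.187, p1 = 0.95 × 0.187 = 0.17765 and R0 = 2.
- V = p1(1 − p1) + R0²·p2(1 − p2) = 0.754.
- Constrained rates under R0 = 2 are 0.2370 and 0.1185, so V0 = 0.599.
- n = 131.0 per arm, total 262. Then 262/0.9 = 291.1, and 292 keeps the arms equal.

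Both stated figures reproduce with an unadjusted, unstratified ratio test.

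**2. Unadjusted power at 131 per arm, log-ratio scale.**
- SE = √[0.823/(131 × 0.177) + 0.813/(131 × 0.187)] = 0.262.
- (ln 2 − ln(0.177/0.187))/0.262 = 0.748/0.262 = 2.855.
- Power = Φ(2.855 − 1.960) = Φ(0.895) = 0.81.

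**3. Adjusting for one baseline score.** The article gives no association between APACHE II and death, so the AUC is assumed and a range shown. Each row rests on 4,000 simulated trials of 262 patients, with a normally distributed score acting linearly on the logit. The crude log risk ratio is compared with a marginal risk ratio standardised from a logistic model. Noninferiority is declared when the upper 95% limit is below 2.

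| Assumed AUC | Variance ratio r, adjusted/crude | Power, crude | Power, adjusted | 262 × r |
|---|---|---|---|---|
| 0.58 | 0.995 | 0.808 | 0.805 | 261 |
| 0.66 | 0.96 | 0.810 | 0.829 | 252 |
| 0.73 | 0.89 | 0.813 | 0.846 | 233 |
| 0.78 | 0.83 | 0.805 | 0.868 | 217 |
| 0.82 | 0.77 | 0.808 | 0.884 | 202 |

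The last column is the number of patients who, analysed with adjustment, would give the precision of 262 analysed crudely. Simulation error on each power is about √(0.81 × 0.19/4000) = 0.006. As a check, Φ(2.855/√r − 1.960) gives 0.83, 0.86, 0.88 and 0.90 for r = 0.96, 0.89, 0.83 and 0.77. That is at most about 2 points above the simulation, and the simulated figures are the ones used here. Type I error at a true ratio of 2 was about 0.025–0.03 for both analyses.

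**4. Using the strata alone.** The strata are unnamed. For illustration they are taken as five centres of near-equal size, with mortality spreads that are also assumed (10,000 simulated trials each; crude ratio against Mantel-Haenszel ratio).

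| Assumed centre mortality | Power, crude | Power, stratified | Type I, crude | Type I, stratified |
|---|---|---|---|---|
| 18.7% in all | 0.813 | 0.810 | 0.027 | 0.027 |
| 10–28% | 0.813 | 0.819 | 0.026 | 0.029 |
| 5–33% | 0.819 | 0.834 | 0.021 | 0.027 |

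Strata alone are worth about 0–1.5 points of power. The crude test is mildly conservative only at the widest spread. Nearly all of the possible gain comes from the severity score.

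**The case against.** The strongest reply is that nothing here is wrong. An unstratified test after stratified randomisation keeps its error rate, chance imbalance is already covered by that error rate, and 262 patients give the planned 80% power without adjustment. All of that stands. The effect of the strata is small, the size of the APACHE II gain is assumed, and at an AUC near 0.58 there is none. With an unknown number of strata and about 48 deaths, a model holding every stratum could be unstable, so the remedy needs a pooling rule. The article also promises confidence intervals without naming a method, so an adjusted interval may stand in a plan that is not shown. It would, however, sit beside a primary test that section 11.1 fixes as crude.

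A reader might infer more than the documents support:
- **That the primary analysis is invalid or the trial too small.** The type I error figures and the exact reproduction of 262 and 292 speak against both.
- **That randomisation is stratified by centre.** The article gives five centres and stratified allocation, but does not connect the two.
- **That APACHE II is the strongest recorded predictor of death.** Table 3 lists it beside SOFA and adequacy of source control, with no ranking.
- **That section 11's remark on varying ICU mortality shows heterogeneity within this trial.** It is given there as the reason for an interim review of the sample size.

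**Conclusion.** The point holds as a matter of efficiency. The article fixes tests that cannot use the randomisation strata or a prognostic score it already collects. At 131 evaluable patients per arm, power is about 81% crude and about 83–88% adjusted, a variance reduction of 4–23%, if the score's AUC for 30-day death lies between 0.66 and 0.82. There is no gain near 0.58, and strata alone give about 0–1.5 points.

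These figures rest on the article's mortality rates, on assumed prognostic strength, on a correctly specified model for the score, and on APACHE II being a baseline value, which is inferred from section 5. They also take the comparison with a ratio of 2 as the test of interest, as the sample size does. That a plain chi-square test addresses equality and not that margin is a separate and larger fault of section 11.1, and this point does not depend on it. The benefit is moderate and uncertain and the cost low, so the change should be made but is not essential to validity.

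**What to change.** - **Section 5:** name the stratification factors, and state that the APACHE II value used is the baseline one as section 11 defines baseline.
- **Section 11.1:** replace the crude test with a marginal risk ratio for 30-day mortality and its 95% confidence interval, the upper limit compared with 2. Standardise it from a logistic model with treatment, randomisation strata and baseline APACHE II. State in advance how sparse strata are pooled and how the standard error is obtained. Give a strata-weighted Mantel-Haenszel or Miettinen-Nurminen ratio as the sensitivity analysis.
- **Section 11.2:** analyse total response by Cochran-Mantel-Haenszel over the same strata.
- **Timing:** fix this before outcome data are seen, ideally before the interim analysis at 50% of the data.

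The scale and margin of section 11 are unchanged, and no new data or patients are needed. The cost is analysis-plan wording, some programming, and reliance on a working model for the primary estimate, which the stratified sensitivity analysis checks.

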## Effectiveness evaluation

8

The primary efficacy end point is the all-cause 30-day mortality of patients in clinically evaluable and microbiologically evaluable populations.

The secondary efficacy endpoints are as follows: (1) the proportion of patients with a total response (composite endpoint consisting of clinical cure and microbiological response) in the clinically evaluable population at the end of treatment (days 5–14) and the test of cure visits (days 12 ± 2); (2) the proportion of total responsive patients in the microbiome-evaluable population at the end of treatment and the test of cure visits; (3) the proportion of microbiologically evaluable patients in the population with a total response to each pathogenic bacterium at the end of treatment and the test of cure visits; (4) the total response proportion of patients with drug-resistant bacterial infections in the microbiome-evaluable population at the end of treatment and the test of cure visits; (5) ICU hospitalization time and expenses; (6) quality of life outcomes or functioning after ICU discharge as assessed by application of the EuroQol-5D and Barthel Index scales; (7) changes in Sequential Organ Failure Assessment (SOFA) scores, reflecting the impact of the treatment on organ dysfunction over time; and (8) time to clinical improvement, measured from the start of treatment until the first observation of significant improvement in clinical status.

Given the variable susceptibility of MDR pathogens to tetracyclines, our study protocol will include analyses stratified by bacterial species. Specifically, subgroup analyses will be conducted for CRAB and CRE to gain a deeper understanding of the comparative efficacy of eravacycline versus tigecycline.

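### The blinded assessor's rating stands beside the unblinded investigators' ratings without deciding status, so the claimed freedom from bias does not hold for clinical cure within total response

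*Protocol article*

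**What the plan says.** All of the blinding text is in section 5 (Test group) of the protocol article.

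- The threat is conceded: "we recognize the possibility of bias resulting from the clinicians’ awareness of the treatment allocation".
- The remedy is announced: "we will include a blinded clinical assessor who will be unaware of the treatment assignments".
- The assessor is to evaluate patients independently, while also "providing objective measurements in conjunction with the evaluations conducted by the investigators".
- The effect claimed is: "This supplementary measure guarantees that a crucial element of our study remains free from bias". The element is not named.
- Blinding otherwise covers only two groups: "ensuring that neither patients nor data analysis researchers are aware of the treatment groups".

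Section 8 (Effectiveness evaluation) makes 30-day all-cause mortality the primary endpoint. Secondary endpoints 1 to 4 all use total response, a "composite endpoint consisting of clinical cure and microbiological response". They apply it in the clinically evaluable population, in the microbiologically evaluable population, by pathogen, and in drug-resistant infections. Secondary endpoint 8 is the time to the first observed significant clinical improvement.

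**The concern.** Clinical cure and significant improvement are judgements made at the bedside. If a clinician who knows the drug contributes to them, expectations about the drug can move the rating. Such expectations are plausible here: the abstract presents the trial as a search for a better option than tigecycline, and the Discussion stresses tigecycline's resistance problem and boxed warning against eravacycline's promise.

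The article sees this risk and provides a blinded assessor, but then has that person's evaluations used together with the unblinded ones and says nothing to make the blinded reading count. A result formed from a blinded and an unblinded rating is not free from bias, so the guarantee does not follow from the mechanism described. At stake is the credibility of the four total-response endpoints and possibly of time to improvement. Mortality as the primary result is not at stake.

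**Working it through.** **1. Text against text (section 5 with section 8).**

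| Question | What the article gives |
|---|---|
| Who knows the allocation? | Treating clinicians and investigators |
| Who does not? | Patients, data analysts, the added assessor |
| How is the assessor's rating used? | Independently made, and used alongside the investigators' evaluations |
| Whose rating defines clinical cure? | Not stated |
| What is claimed? | A guarantee of freedom from bias for an unnamed element |
| Which endpoints need a clinical judgement? | Total response through clinical cure (secondary 1 to 4); time to improvement (secondary 8) |
| Which do not? | 30-day death |

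The stated joint use leaves a route for the unblinded rating into clinical cure. The guarantee would hold only if that route were closed.

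**2. The plan's own figure, which the concern leaves unchanged.** Section 11 (Statistics) gives control mortality 18.7%, true ratio 0.95, noninferiority ratio 2, one-sided 0.025 and 80% power. With the Farrington-Manning score method:

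- p2 = 0.187, p1 = 0.95 × 0.187 = 0.17765, d = 2 × 0.187 − 0.17765 = 0.19635
- constrained rates under the null: 0.2370 and 0.1185
- null variance: 0.2370 × 0.7630 + 4 × 0.1185 × 0.8815 = 0.5986
- alternative variance: 0.17765 × 0.82235 + 4 × 0.187 × 0.813 = 0.7542
- n per arm = (1.960 × √0.5986 + 0.842 × √0.7542)² / 0.19635² = 131.0

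That is 262 in total, and 262 / 0.9 gives 292 after rounding up to whole patients, as stated. This size is for mortality and does not depend on who rates cure.

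**3. Illustration of what a rating shift could do.** The article gives no response rate and no size of bias, so every value in this step is an assumption. Take no true difference, n per arm, response rate p, and a shift b added to one arm by unblinded rating. The rejection probability of a two-sided 5% test is about Φ(b/SE − 1.96) + Φ(−b/SE − 1.96).

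With p = 0.75, b = 0.05 and SE = √(2p(1 − p)/n):

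- n = 131: SE = √(0.375/131) = 0.0535, b/SE = 0.935, rejection probability 0.154
- n = 80 (assumed smaller evaluable set): SE = √(0.375/80) = 0.0685, b/SE = 0.730, rejection probability 0.113

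Range over other response rates, with n = 131 and each arm's variance taken at its own rate:

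| Response rate | Shift of 2 points | Shift of 5 points |
|---|---|---|
| 70% | 6.5% | 14.8% |
| 80% | 7.0% | 18.7% |
| 90% | 8.7% | 33.9% |

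Two features make these figures lean high. The evaluable populations in section 7 are culture-positive, protocol-adherent subsets, so n may be below 131 per arm, and the same shift then inflates the error less. The calculation also carries the whole shift into total response, although that composite requires a microbiological response as well.

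**The case against.** The strongest reply is that the assessor's evaluations are expressly called independent. The sentence can describe two assessments side by side, and nothing says that they are merged or that the investigator's rating decides an endpoint. This stands as far as it goes. A reader might infer that the blinded rating is subordinate, or that the unblinded rating determines clinical cure; the article says neither. It says that the two are used together and does not say which one counts.

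A second reply is that an adjudication rule is commonly left to a fuller protocol or analysis plan. That is also fair, and the absence of such a rule is not the point made here. The point rests on what section 5 does state: joint use with unblinded ratings, and a guarantee which that joint use cannot deliver.

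A reader might also look to section 4.3 (Criteria for early withdrawal from treatment), where "the clinical efficacy is evaluated by the researcher as persistent or progressive", as proof that unblinded staff score efficacy. It is not. That criterion concerns stopping study treatment when a resistant strain is cultured, not the scoring of cure or improvement, and it gives no support here.

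Finally, it is tempting to quote a larger error rate. An assumed 10-point shift at 75% response and 131 per arm gives about 46%. The arithmetic is right, but no source in the article supports a shift of that size, and it treats the planned blinded assessor as having no effect at all.

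**Conclusion.** The concern holds in limited form. Section 5 couples the blinded evaluations with unblinded ones, gives the blinded rating no deciding status, and still guarantees freedom from bias. The unblinded rating can therefore enter clinical cure, and through it secondary endpoints 1 to 4. For time to clinical improvement the exposure is possible but less clear, because the article does not say who observes the improvement. Ascertainment of 30-day death and the sample size of 262 are unaffected.

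The size cannot be determined from the article. About 15% instead of 5% (about 11% with 80 per arm) is an illustration that assumes 75% response, no true difference, a 5-point shift in one arm and full carry-over into total response. It shows that a modest shift would matter, not that such a shift will occur. The point deserves correction because the safeguard is already planned and is not put to use where it is needed.

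**What to change.** 1. State in section 5 or section 8 that the blinded assessor's determination defines clinical cure, and hence the clinical part of total response, at the end-of-treatment and test-of-cure visits.
2. Keep the investigators' ratings for care decisions and use them for a sensitivity analysis of total response.
3. For time to clinical improvement, use the blinded rating where it is already scheduled; otherwise report this endpoint as assessed without blinding.
4. Replace the guarantee with a statement that the measure reduces the risk of assessment bias, and name the endpoints it covers.

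Items 1, 2 and 4 need wording and a field in the case report form for the blinded determination. They add no staff, provided the assessor's evaluations cover the two visits, which the article does not specify. Item 3 is worded as a choice because the article gives no frequency for the blinded assessments: requiring blinded ratings throughout 4 to 14 days of treatment at 5 centres could mean repeated extra assessments, which cannot be assumed to be free. The rule should be in place before patients are rated, since a blinded determination that was not recorded cannot be recovered at analysis.
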